# Summary

This proposal describes a collaborative study between the UK Public Health Rapid Support Team (UK-PHRST), London School of Hygiene and Tropical Medicine (LSHTM), and Kenema Government Hospital (KGH), Sierra Leone to develop and validate a novel enzyme-linked immunosorbent assay (ELISA) to investigate antibody responses to Lassa virus (LASV) infection in oral fluid samples.

The study will compare oral fluid and blood samples from Lassa Fever (LF) survivors and unexposed controls in order to validate oral fluid samples as a means of establishing anti-LASV antibody prevalence in endemic settings.

There is limited recent evidence on the prevalence of LASV infection and the longevity of immune responses to LASV within endemic communities. A robust antibody assay suitable for use with non-invasive oral fluid sampling could greatly improve ability to accurately estimate prevalence of infection, describe the spectrum of disease, and facilitate longitudinal incidence, immunity and transmission studies through improved acceptance of testing.

A prototype ELISA for use with oral fluid has been created in the UK by experts in this form of testing. A small number of stored convalescent human samples (n=6) from Sierra Leone consented for research purposes will be obtained through official channels to finalise the prototype development in the UK. Validation of the assay, including determination of sensitivity and specificity, will be done in Sierra Leone by national laboratory staff supported by UK-PHRST laboratory scientists, using oral fluids and blood samples collected from individuals confirmed to have had LF by the Lassa Fever Unit of KGH, Kenema, Sierra Leone. Samples from individuals without LF diagnosis or known LASV exposure will be collected as controls.

A validated non-invasive, community-acceptable, and logistically simpler tool for measuring LASV sero-prevalence and sero-conversion in communities in endemic countries will greatly facilitate the understanding of LASV epidemiology and support the development and trialling of LASV vaccines and other control measures.

# Introduction

Lassa Fever (LF) is a viral haemorrhagic illness endemic in parts of West Africa including Sierra Leone, Liberia, Guinea, Mali and Nigeria where the illness was first identified.^1^ In endemic settings, it is believed that the majority of those infected with Lassa virus (LASV) experience sub-clinical infection or mild disease with only around 20% infections resulting in hospitalisation.^2^ Overall mortality from infection is thought to be ~1% but in hospitalised cases, case fatality rates of up to 50 to 70% have been reported,^3^ often linked to late presentation. LF outbreaks can cause significant public health emergencies, often triggered by patients presenting in health facilities that are unaccustomed to receiving haemorrhagic fever cases, with the accompanying risks of health worker and nosocomial infection, as well as the burden of investigating and managing large numbers of suspect cases.

During clinical LASV infection, early symptoms may include fever, headache, and muscle aches, mimicking symptoms of diseases such as malaria and typhoid fever which are common in LASV endemic areas. As clinical infection progresses, patients may go into shock, develop multi-organ failure, and sometimes bleed from the mouth, nose, eyes, or rectum.^4^ In addition, there is evidence that LF survivors suffer long-term sequelae such as hearing loss, depression, joint pain and hair loss.^3^ There are currently no vaccines to prevent LF nor approved drugs to treat, and although accepted wisdom is that early clinical use of the nucleoside drug ribavirin can reduce mortality in clinical cases, there is little scientific evidence to support this.

It is estimated that up to 300,000 LASV infections occur annually resulting in 5,000 deaths,^2^ but these data are based largely on the results of a single study carried out in the 1980s.^5^ Similarly, there is little evidence for the 20-80% proportions cited for sub-clinical and clinical disease. The need for more robust estimates based on up-to-date data has been recently emphasised by WHO in its Research & Development Blueprint which identified LASV as one of eight priority diseases for urgent attention.^6^ More precise estimates of these parameters, and deeper understanding of the exposure and immune status of populations in the endemic countries, will also be critical to developing, targeting, and evaluating the efficacy of LASV vaccine candidates and other control measures.

LASV is an arenavirus composed of an enveloped, segmented negative single-stranded RNA and classified as a Category A pathogen requiring high biosafety handling.^7^ Several methods are used to diagnose LF cases including reverse transcriptase polymerase chain reaction (RT-PCT), a recombinant LASV (ReLASV) ELISA, as well as antigen detection tests and a lateral flow immunoassay rapid diagnostic test, all of which require blood samples.^8^ Virus isolation by cell culture is the gold standard for LASV diagnostic purposes, but cannot be performed in normal diagnostic facilities due to the high-level biosafety laboratory facilities required for live virus work.

## 2.1 Host & transmission

The natural host for LASV is the common African soft-furred rat, *Mastomys natalensis*, in which infection is thought to be lifelong and harmless. Recently there have been reports of other host rodents and investigations into this are continuing.^9^ Viral transmission occurs - via aerosol or contact - from infected rats or their excretions to humans, and subsequent LASV infection in humans can be lethal. The virus can also be transmitted between humans via blood and tissue fluids, particularly in hospitals with weak infection prevention control measures, and among contacts exposed to body fluids through caring practices, resulting in high mortality rates.^3, 10^

## 2.2 Sero-prevalence & incidence of infection

At present, sero-prevalence and persistence of LASV antibodies and incidence of infection (measured by sero-conversion) can only be studied through surveys using blood-based sampling. Significant bio-security, community and psycho-social issues accompany the collection of blood samples in affected countries. Indeed, the drawing of blood can be one of the most contentious issues in a clinical trial process potentially arousing political, cultural and social antipathy,^11-14^ as well as requiring considerable logistics to correctly and safely collect and store specimens.

“Oral fluid” is found in the gingival crevice (between teeth and gums) and contains considerably higher levels of IgG than saliva.^15^ Oral fluid sampling has major advantages over blood collection: it is non-invasive, more acceptable to subjects of all ages (due to absence of pain and low or no perceived risk of contamination), and easier to collect without the need for medically-trained personnel. It is safer for collectors, removing the risk of needle-stick injury and other collection and storage-related exposures.^16^

The availability of a non-blood-based, non-invasive alternative method to detect LASV antibodies, and thus past infection, would allow more comprehensive sampling due to its higher acceptability by populations. This would greatly facilitate the community-based research needed to gather critical information on the full burden of LASV infection and disease and on levels of immunity, while also potentially providing a non-invasive tool to track responses to immunisation when trials are underway.

Oral fluid has been used in surveillance activities to detect antibodies to viral infections such as mumps, measles, rubella, and is routinely used for the diagnosis of HIV and Hepatitis A and C.^15, 17^ During the 2013-16 West Africa Ebola outbreak, a reverse IgG-capture ELISA for oral fluid samples was developed by the Public Health England (PHE) team involved in this proposal, and used to investigate the sero-prevalence of Ebola virus infection in affected households and communities, with high sensitivity (97.4%, 95% CI, 92.5%-99.5%) and specificity (99.7%, 95% CI, 98.4%-99.7%).^18^

**2.3 Assay development**

Laboratory scientists from Public Health England and Imperial College are in the process of developing a prototype LASV immunoassay for use with oral fluid incorporating single or combined LASV antigens (glycoprotein 1 (GP1), GP2 or recombinant matrix protein (rMP)). To complete the development stage and provide a reliable assay for validation, a small number of anonymous convalescent human samples will be requested from the KGH LF unit under a Material Transfer Agreement. Once the assay kits are complete, all subsequent validation work will be done in Sierra Leone in order to support increased research capacity in country.

**2.4 Study sites**

Kenema District is one of the ‘hotspots’ of Lassa Fever transmission in Sierra Leone and the KGH LF Unit is the national centre for diagnosis, treatment and research. Together with the Irrua Specialist Teaching Hospital in Nigeria, KGH is one of only two facilities globally where LASV testing and LF patient admission is continuous, and there is a programme of survivor monitoring and follow-up, which will facilitate the recruitment of the convalescent LF survivors needed for this validation work.

The KGH laboratory, medical and outreach teams at KGH have extensive experience of diagnosing treating and collecting data on LF, supported over many years by partners including Tulane University, New Orleans, USA. KGH carries out clinical and diagnostic research including an ongoing 5-year study of sequelae and immunity in survivors of viral haemorrhagic fevers (referred to hereafter as the Survivors Study). This validation study will be embedded in the Survivors Study for efficiency and to ensure a coordinated approach to survivors. The study presented here shares a principal investigator ([name]) with the Survivors Study and the study teams will collaborate on all activities.

# Aims and objectives

The aim of this study is:

- To develop and examine the validity of a new assay to measure evidence of LASV infection for use with oral fluids by comparing naturally acquired antibody responses to LASV in oral fluids and blood serum samples from LF survivors and unexposed controls.

The specific objectives are:

1. To complete the development of a novel ELISA to investigate naturally acquired antibody responses LASV infection in non-invasive oral fluid samples
2. To validate this tool and determine its sensitivity and specificity by measurement of LASV-specific antibodies in oral fluids and blood samples from LF survivors and unexposed controls
3. To evaluate the feasibility of oral fluid as an alternative sampling tool using these findings
4. In LF survivors, to correlate LASV-specific antibody responses with time since clinical infection, original clinical characteristics and potential re-exposure events.

# Methods

## 4.1 Recruitment

**Inclusion Criteria**

For LF survivor participants

- History of LF as documented by a positive anti-LASV Ag or IgM ELISA in the KGH diagnostic laboratory
- Age ≥6 years
- No fever at recruitment (Temperature below 37.5^o^C)
- Willingness to provide informed consent (or assent, if applicable)
- Willingness to undergo phlebotomy for blood samples and provide oral fluid samples

For unexposed control participants

- No history of LF clinical illness and/or LASV positive test,
- No history of residence, work or visiting in LF endemic zones
- No history of contact with a LF case
- Age ≥6 years
- No fever at recruitment (Temperature below 37.5^o^C)
- Willingness to provide informed consent (or assent, if applicable)
- Willingness to undergo phlebotomy for blood samples and provide oral fluid samples

## 4.2 Study participants

Up to 70 LF survivors admitted to the KGH Lassa Ward for treatment of confirmed LF and discharged up to 15 years prior to the start of this study will be recruited. The study team will work with LF programme outreach staff at KGH to identify LF survivors and implement the study protocol.

Unexposed controls will be recruited from among individuals understood to have no exposure to the *Mastomys natalensis* rodent or LF cases. After agreement with the relevant authorities, control participants will be sought from among medical and/or nursing students in Freetown (an area considered outside the LASV endemic zone) as a relatively easily-accessed cohort of individuals for whom taking part in a research study may be of interest. The study brings no inherent benefit to participants, however those involved in study for health care/public health careers may benefit from taking part in a well-conducted research study. We will also collaborate with college authorities to offer lectures on the conduct of research studies and on LF as one of Sierra Leone’s priority emerging disease issues. A questionnaire including past travel/residence/contact information will be used to exclude candidates with possible exposure (Appendix 2: Control eligibility check).

## 4.4 Eligibility & consent

After holding meetings with key community leaders and Lassa survivor communities about the aims of the study, individual survivors will be approached for recruitment. The purpose and objectives of the study will be explained verbally, and a patient information leaflet provided for those able to read (Appendix 3: Patient information leaflet). Study investigators will explain the role of the participant in the study and discuss potential risks of participation. Informed consent will be in English. If English is not the patient’s native language or they are unable to read, the patient will be informed about the study and related risks in his or her native language by a collaborating investigator fluent in that language who will read the consent form to the potential participant in the presence of a witness.

Potential participants will have the opportunity to raise any concerns, after which, written informed consent will be sought from all adult participants and from adult guardians of child participants (Appendix 1: Consent form). For survivors, consent will include approval to access clinical records of their LF admission and to information previously given to the Survivors Study. All participants will be asked to consent to storage of their oral fluid and blood samples for possible future research; samples from participants who do not agree to storage will be destroyed after the validation study.

Following provision of informed consent, clinical, demographic and risk factor information for the participant will be collected from medical records completed during admission and from the Survivor Study database. Participants will be asked to respond to a short questionnaire specific to the validation study focussing on possible antibody-boosting exposures (Appendix 2: Questionnaires). Data will be entered into a password-protected electronic database.

## Sample collection

A 5ml blood sample will be collected and stored in a cool box for daily transfer to the laboratory. Serum will be processed then stored at -20°C prior to testing antibody responses.

Oral fluid will be collected by the participant rubbing a small sponge swab firmly on the gums for 90 seconds, then placing it in a stoppered plastic tube and in a sealable plastic bag and stored in a cool box, then transferred for storage at -20°C at the end of the day prior to testing antibody responses. Experience suggests that oral fluid collection is acceptable to participants of all ages.^18^

Oral fluid and blood samples will be tested to detect anti-LASV antibodies using the new ELISA tool. Further comparative tests may be conducted with assays currently in use in KGH.

## Data collection

Data will be collected using a study-specific questionnaire (Appendix 2), participants’ medical records during admission to KGH Lassa Fever Unit, and data held in the Survivors Study database. Variables for survivors will include demographics, symptoms and clinical information at the time of admission, dates of LF onset and discharge, laboratory test results at discharge, and information on any known exposure to LASV or LF patients since recovery, in order to explore potential immunity-boosting events.

Unexposed participants will be asked a series of questions regarding exposure to LASV hosts and/or cases to determine if they fulfil the inclusion criteria, and if not excluded based on responses, will be asked to respond to a brief demographic questionnaire.

Both groups will be asked to give feedback on using the oral fluid swab, including perceptions of the method as a follow-up and research tool.

## Sample size

We will recruit at least 70 LF survivors and 70 unexposed controls. This will allow for an estimation of specificity of at least 61.2% at 95% confidence interval (CI) with10% relative precision if true sensitivity is 85%, and higher precision if true sensitivity is greater (Table 1).

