**Table 1: Sample size estimation for a range of sensitivity levels**

| Sensitivity point estimate (%) | Relative precision (%) | | | |
| --- | --- | --- | --- | --- |
|  | 5 | 10 | 20 | 50 |
| 80 | 385 | 97 | 25 | 4 |
| 85 | 272 | 68 | 17 | 3 |
| 90 | 171 | 43 | 11 | 2 |
| 95 | 81 | 21 | 6 | 1 |

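### The sample-size sentence gives a 61.2% bound for specificity that does not follow from Table 1; the table supports an expected lower limit of 76.5% for sensitivity, and no precision is stated for specificity

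*Protocol*

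**What the plan says.** The Sample size section of the protocol sets the target: "We will recruit at least 70 LF survivors and 70 unexposed controls". It then says this permits "estimation of specificity of at least 61.2% at 95% confidence interval (CI) with10% relative precision if true sensitivity is 85" per cent, with better precision if sensitivity is higher, and refers to Table 1.

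Table 1 is titled "Sample size estimation for a range of sensitivity levels". Its rows are sensitivity values of 80, 85, 90 and 95%, and its columns are relative precisions of 5, 10, 20 and 50%. The 85% row reads 272, 68, 17 and 3. No row or column concerns specificity.

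Specificity is nonetheless a stated target. The second specific objective is "To validate this tool and determine its sensitivity and specificity by measurement of LASV-specific antibodies in oral fluids and blood samples", and the Data analysis section lists sensitivity and specificity first.

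Section 4.2 words the survivor number differently: "Up to 70 LF survivors admitted to the KGH Lassa Ward".

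**The concern.** Sensitivity is estimated in survivors and specificity in controls. The sentence puts a lower bound on specificity, makes it conditional on an assumed sensitivity, and cites a table about sensitivity. These cannot all belong to one calculation. The value is also suspect, because 10% relative precision around 85% cannot reach as low as 61.2%.

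This sentence is where the protocol tells ethics reviewers and readers what 70 per group will deliver. As printed, it gives a wrong figure under the wrong name. It also leaves the 70 controls without any valid statement of precision, in a study meant to support an assay for sero-prevalence surveys, where false positives matter.

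**Working it through.** **Inputs.** From the Sample size section: 95% confidence (taken as two-sided, z = 1.96, which reproduces Table 1), relative precision r = 10%, assumed sensitivity p = 85%, n = 70 per group. From Table 1: n = 68 for p = 85% and r = 10%. No assumed specificity is given.

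**1. Reproduce Table 1.** The formula is n = z²(1 − p)/(p r²), rounded up. For p = 0.85 and r = 0.10:

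n = 3.8416 × 0.15 / (0.85 × 0.01) = 67.79, so 68.

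The same formula gives every cell:

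| Sensitivity | r = 5% | 10% | 20% | 50% |
| --- | --- | --- | --- | --- |
| 80% | 385 | 97 | 25 | 4 |
| 85% | 272 | 68 | 17 | 3 |
| 90% | 171 | 43 | 11 | 2 |
| 95% | 81 | 21 | 6 | 1 |

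All 16 agree, so the planning method is known: a normal-approximation (Wald) interval for one proportion.

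**2. The lower limit that goes with n = 68.** p(1 − r) = 0.85 × 0.90 = 76.5%. At n = 70 the half-width is 1.96 × √(0.85 × 0.15/70) = 8.36 points. The interval is 76.6 to 93.4%, and the relative precision is 8.36/85 = 9.8%.

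**3. Try to obtain 61.2%.**

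- Other intervals at n = 70: the Wilson lower limit at 85% is 74.8%, and the exact (Clopper-Pearson) lower limit for 60/70 is 75.3%.
- Higher confidence, Wald at n = 70: the lower limit is 74.0% at 99% confidence and 68.4% at 99.99%.
- As a lower limit on 85%: (85 − 61.2)/85 = 28% relative precision, which needs 3.8416 × 0.15/(0.85 × 0.0784) = 8.6, about 9 participants.
- As a specificity point estimate: with 70 controls the half-width is 1.96 × √(0.612 × 0.388/70) = 11.4 points, or 18.7% relative precision. Ten per cent would need 3.8416 × 0.388/(0.612 × 0.01) = 243.5, so 244 controls.

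None of these matches the sentence. Two coincidences do give the number: 68 × 0.90 = 61.2 (10% taken off the sample size) and 85 × 0.9 × 0.8 = 61.2. Neither can be confirmed from the protocol.

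**4. What 70 controls give.** The protocol assumes no specificity, so these results are illustrative (exact 95% intervals):

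| Negative controls | Observed specificity | 95% CI |
| --- | --- | --- |
| 70/70 | 100% | 94.9 to 100% |
| 68/70 | 97.1% | 90.1 to 99.7% |
| 66/70 | 94.3% | 86.0 to 98.4% |

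**5. Ceiling or floor of 70 survivors.** At p = 85%, 68 evaluable survivors give 9.98% relative precision. With 67 it is 1.96 × √(0.15/(0.85 × 67)) = 10.06%. Fewer than 68 therefore misses the stated 10%, though only slightly at first.

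**The case against.** The best defence is that Table 1 is the real justification, and it is correct. It asks for 68, the plan recruits 70, and neither recruitment nor analysis depends on the 61.2%. That stands: the fault is a wrong sentence beside a sound calculation, and the design does not fail.

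It can also be said that the formula applies equally to the controls. With n = 70 it gives 10% relative precision or better for any true specificity of at least 3.8416/(3.8416 + 70 × 0.01) = 84.6%. That is true, and a fuller treatment of specificity may sit in an analysis plan that is not shown. But the protocol does print a figure for specificity, and that figure is wrong. Correcting it asks for nothing that is normally left to a later document.

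Three stronger readings are tempting, and the protocol does not support them.

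- A reader might infer that the study claims only that specificity exceeds 61%, so that the assay would be useless for surveys. The sentence describes what the sample can estimate; it sets no performance claim or acceptance threshold.
- A reader might argue from predictive values. These depend on a prevalence that the protocol does not give, so a single assumed value would prove little.
- A reader might take 76.5% as an assured minimum. It is the Wald limit expected when the estimate is about 85%. If true sensitivity is 85% and n = 70, the Wald lower limit reaches 76.5% in only about 52% of studies.

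**Conclusion.** The point holds as a wrong figure in the sample-size justification. The printed 61.2% follows neither from Table 1 nor from any standard interval for 70 participants, and it is attached to specificity although its condition and its source concern sensitivity. By the table's own method the expected lower 95% limit is 76.5% for sensitivity, 15.3 points higher; exact or Wilson limits at n = 70 are about 75%. No assumed specificity or resulting precision is stated for the 70 controls.

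The 76.5% assumes that the authors meant a two-sided 95% Wald limit at 85% sensitivity, which is the calculation Table 1 contains. The mismatch in value and parameter does not depend on that assumption, nor on how 61.2% arose. The planned 70 per group is consistent with Table 1 and needs no change on this account.

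**What to change.** Replace the sentence with text such as:

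*With 70 evaluable survivors and an observed sensitivity of about 85%, the expected 95% CI is 75.3% to 92.9% (exact method, 60/70). For planning, the Wald method of Table 1 gives 76.6% to 93.4%, a relative precision of 9.8%. For the 70 controls, exact 95% CIs for illustrative results are 94.9% to 100% for 70/70, 90.1% to 99.7% for 68/70 and 86.0% to 98.4% for 66/70.*

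Use one interval method for both parameters when reporting. The draft uses exact limits and keeps the Wald figure only as the link to Table 1. Mark the specificity results as illustrative assumptions, or replace them with a specificity the sponsor can justify.

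Reconcile the survivor number in section 4.2 (a ceiling) with that in the Sample size section (a floor), and say that the precision refers to evaluable survivors, since 68 are needed for 10% at 85%.

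The cost is a few sentences of protocol text. No extra participants, samples or analyses are needed.
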